### Positive affect intervention

Affect regulation treatment to enhance methamphetamine intervention success (ARTEMIS) is a multi-component, individually-delivered 5-session intervention targeting positive affect regulation. This intervention was adapted from prior clinical research testing the feasibility and acceptability of a positive affect intervention for recently diagnosed HIV-positive persons [37]. The extant positive affect intervention protocol was adapted and pilot tested in a RCT with 21 methamphetamine-using MSM receiving CM [36]. Based on the results of the pilot RCT, the positive affect intervention protocol was further refined prior to initiating the present Phase II RCT with HIV-positive, methamphetamine-using MSM.

The original positive affect intervention protocol consists of eight skills:

(1) positive event noting; (2) positive event capitalizing; (3) gratitude; (4) informal and formal mindfulness; (5) positive reappraisal; (6) personal strengths; (7) attainable goals; and (8) acts of kindness. As shown in Table 1, we modified the original protocol to tailor this positive affect intervention for HIV-positive, methamphetamine-using MSM. These adaptations included additional content to optimize delivery of the core positive affect regulation skills with this population and new components designed to facilitate greater engagement in the recovery process (e.g., problem-focused coping, values clarification, and referral to community-based services). Informed by prior research examining the efficacy of mindfulness-based relapse prevention [38–40], participants also complete meditation exercises during ARTEMIS intervention sessions to further enhance metacognitive awareness and assist individuals in coping more effectively with methamphetamine withdrawal. Self-report measures of stimulant craving before and after each session as well as a measure of positive and negative affect before sessions one, three, and five are completed by participants. Participants can choose to receive $20 in cash per session or two $50 debit cards upon completion of all five sessions, complete detailed home practice exercises, receive a workbook with each of the skills outlined and an iPod shuffle that is pre-loaded with meditation exercises to facilitate regular practice.

**Table 1 Tab1:** Positive affect intervention protocol for HIV-positive, methamphetamine-using MSM

Session	Positive Affect Regulation Skills	Additional Intervention Content
1	Noticing Positive Events	Psychoeducation on Stimulant Withdrawal
	Capitalizing on Positive Events	Capitalizing on Non-Reactive Urine Toxicology
	Gratitude	Breathing Retraining with Positive Event Imagery
2	Mindfulness (Informal and Formal)	Breath Meditation
		Self-Compassion
3	Positive Reappraisal	Problem-Focused Coping & Reasoned Action
		Breath Meditation
4	Strengths	Values Clarification
	Attainable Goals	Mountain Meditation
5	Altruism	Volunteer opportunities
		Linkage to More Intensive Community-Based Services
		Loving Kindness Meditation

Session one begins with an overview of the intervention and psychoeducation about the stressful nature of stimulant withdrawal that individuals experience during CM. Positive affect regulation skills are framed as one way of more effectively coping during this stressful period. Participants are encouraged to start by noticing positive events that occur in daily life and explore ways to amplify or extend the experience of positive emotions related to these events (i.e., capitalizing). In addition to identifying positive events in their daily lives, participants are asked to describe positive emotions that stem from having a urine screen during CM that was non-reactive for stimulants (where applicable) and continue to capitalize on this positive event. The concept of gratitude as a feeling of appreciation or thankfulness that can stem from positive events is also introduced. Finally, facilitators deliver a modified breathing retraining exercise that includes positive event imagery to assist participants with capitalizing on a positive event in vivo. For home practice, participants are asked to complete the “One Good Thing” exercise where they note a positive event that happened each day and briefly describe responses to the event. Participants are also asked to begin keeping a gratitude journal that continues throughout the 5-session intervention [41].

Session two includes mindfulness-based skills training to cultivate non-judgmental, present-centered awareness. By facilitating metacognitive awareness, mindfulness promotes greater insight into cognitive and emotional responses to events which may reduce craving and decrease the likelihood that individuals engage in the overlearned response of substance use [39]. Informal mindfulness exercises are completed in-session to encourage individuals to develop an enhanced awareness of daily experiences (e.g., brushing one’s teeth). Participants also complete a brief formal mindfulness-based meditation practice (i.e., breath awareness) and receive an iPod shuffle preloaded with three meditation exercises: breath awareness, mountain meditation and loving kindness meditation [42]. Finally, this session concludes with a discussion of the importance of self-compassion as a way of coping with stressful life circumstances. Participants are encouraged to be more tolerant of their imperfections by developing a supportive and caring self-orientation. Home practice includes informal mindfulness practice (i.e., “Practicing Being Present in Daily Life” exercise), formal mindfulness meditation using the iPod shuffle, and the gratitude journal. Participants may listen to any of the three recordings on the iPod shuffle.

Session three focuses on executing effective coping responses. Participants are introduced to the concept of positive reappraisal whereby individuals change their interpretations of stressful events to support successful adaptation. The facilitator reviews ways in which changing thoughts about a stressful event (i.e., positive reappraisals) can affect emotional responses and subsequent behaviors. This is generally consistent with the approach of cognitive-behavioral treatments like the Matrix Model [43], but there is no requirement that the initial appraisal of an event is distorted. Especially where aspects of a stressful event are uncontrollable, participants are encouraged to examine ways in which the experience could have been worse or how they learned something new as a result of enduring this stressful event (both examples of positive reappraisals). Participants are asked to identify a recent stressful event and work with the facilitator to practice different methods for positive reappraisal in session.

Another important component of session three is reviewing methods of enhancing coping effectiveness in response to controllable situations [44, 45]. Where aspects of stressful circumstances are controllable, participants are encouraged to explore problem-focused coping strategies that can be implemented to reduce the experience of stress. Participants briefly review possible problem-focused coping strategies with the facilitator. This process of executing effective coping responses by engaging in positive reappraisal and then problem-focused coping is presented as “reasoned action” where managing emotional responses to an event is a critical first step towards addressing any aspects that are within one’s control. Participants also complete a formal mindfulness-based meditation practice (i.e., breath awareness) at this session. Home practice includes daily positive reappraisal exercises where participants identify stressful events, develop positive reappraisal(s), and delineate concrete actions that can be taken to address the identified ‘problem.’ Participants also continue with the meditation practice and the gratitude journal.

Session four begins with an exercise where participants are asked to reflect on personal strengths. This process promotes greater insight into personal sources of resilience and enhances self-affirmation, which has been linked to enhanced problem solving and self regulation [46, 47]. After identifying personal strengths, participants are asked to examine the degree to which these strengths are linked to personal values or the ways in which strengths assist one with living values in action. Then, participants are introduced to the concept of attainable goals, which are presented as short-term goals that are Achievable, have Clear steps, and a definitive Endpoint (ACE). Strengths and values are presented as important resources that energize goal-oriented progress. Participants are encouraged to examine ways in which leveraging personal strengths could facilitate progress toward attainable goals. Values are framed as the underlying meaning structures that remind individuals why attainable goals are important. This session concludes with the mountain meditation which focuses on embracing personal strengths and resilience in the midst of stress [42]. For home practice, participants are asked to monitor progress towards completing attainable goals identified in session while noting personal strengths that assist with progress toward these goals. Participants also continue with the meditation practice and the gratitude journal.

Session five targets altruism by discussing findings that small acts of kindness may enhance psychological adjustment and bolster physical health [48, 49]. Participants review ways in which they can incorporate small acts of kindness into their daily activities and review formal volunteer opportunities available in the community. Participants also complete the loving kindness meditation [42], which focuses on experiencing feelings of love and caring toward another person. The facilitator also leads the participant through a thorough skills review of all the positive affect and coping skills delivered throughout the five sessions. This portion of the intervention focuses on discussing positive aspects of the ARTEMIS sessions for the participant and ways in which he can continue to pursue treatment in the community. Tailored referrals are provided to assist participants with engaging in more intensive mental health or substance abuse treatment.

### Attention-control condition

The attention-control consists of five sessions that include face-to-face administration of psychological measures and neutral writing exercises [50]. Participants are instructed to write as if they were reporting facts without going into any of the thoughts or feelings about the events (e.g., plans for the next 24 h). All sessions are comparable in length to the intervention sessions, but do not include any skills practice. Self-report measures of stimulant craving before and after each session as well as a measure of positive and negative affect before sessions one, three, and five are completed by participants. Participants can choose to receive $20 cash for completing each attention-control session or two $50 debit cards upon of the completion of the fifth session, and an iPod with three preloaded pop songs.

### Staff training and fidelity monitoring

Each staff member receives a detailed training on assessment protocols for this RCT: 1) privacy and confidentiality including HIPAA security practices and human subjects protection training; 2) obtaining informed consent; 3) blood borne pathogens training 4) safe shipping of biological specimens training 5) laboratory safety for researchers training 6) technology training including use of laptops for data collection and the participant database; 7) interviewing techniques such as building rapport, working with diverse populations, cultural sensitivity, population-specific issues and referrals, maintaining confidentiality, basic quantitative and qualitative interview skills; 8) a detailed suicidality assessment protocol; and 9) and role playing of assessments or individual sessions.

Intervention facilitators are provided with a detailed manual that describes the procedures for administering the five individual intervention sessions. Facilitators conducted mock sessions and the audio recordings of these sessions are reviewed by a clinical supervisor who then meets one-on-one with the facilitator to provide feedback on delivery of intervention content and process-oriented techniques. Mock sessions are repeated until the facilitator is judged to be competent with each of the five intervention sessions.

The protocol for monitoring the fidelity of the positive affect intervention sessions during the course of the study includes audio recording of sessions for weekly review with a clinical supervisor and fidelity checklist ratings that are reviewed monthly in group supervision. Audio recordings of intervention sessions are reviewed by the fidelity monitor and the clinical supervisor to assess adherence to the protocol, delivery, interpersonal skills, rapport, and session flow. Approximately 10 % of all positive affect intervention sessions are coded using fidelity rating checklists with detailed feedback provided to facilitators.

### Follow-up assessments and specimen banking

At 3, 6, 12 and 15 months after enrollment in CM, each participant completes computer-based follow-up assessments that are administered by a trained interviewer who has not administered intervention or attention-control sessions to that participant. Self-reported substance use and sexual behavior measures are completed by participants using audio computer-assisted self-interviewing to enhance reliability and validity [51]. Urine samples for on-site toxicology testing for recent use of methamphetamine, cocaine, opiates, marijuana, and benzodiazepines (Redwood Biotech iCup®; Santa Rosa, CA) are collected at each assessment. Peripheral venous blood samples are collected at baseline as well as 6, 12, and 15 months following enrollment in CM to measure HIV viral load and CD4+ T-cell count. Participants receive a pre-loaded $50 debit card for completing each of the assessment visits over the 15-month period.

Participants are also asked to provide an additional 25 ml of peripheral venous blood using two 10 mL EDTA and two 5 mL PAXgene® tubes (Qiagen, Inc.) at baseline as well as 6, 12, and 15 months following enrollment in CM. Using EDTA tubes, leukocyte DNA is extracted and banked. Approximately three mL of plasma are also banked. PaXgene® tubes are used for isolation and stabilization of RNA. These tubes are progressively frozen and banked.

### Primary and secondary outcome measures

#### HIV viral load

HIV viral load testing is performed to detect plasma HIV RNA using the Abbott RealTime HIV-1 assay (Abbott Molecular, Inc.; Des Plaines, IL). Although this assay has a lower limit of detection of 40 copies/mL, valid viral load values below this level are observed with less reliable frequency [52]. The primary outcome for this RCT is change in mean log_10_ HIV viral load. Sustained HIV viral suppression, defined as an undetectable HIV viral load (<40 copies/mL) over the 15-month follow-up, will be examined as a secondary outcome.

#### CD4+ T-cell count

CD4+ T-cell count is measured with whole blood using flow cytometry. CD4+ assays are performed by Quest Diagnostics.

#### ART adherence and persistence

At each assessment, participants currently taking ART medications are asked to rate their adherence to each medication during the past 30 days using the visual analogue scale [53]. Participants are also asked to indicate if they have experienced a treatment interruption, a period of two days or more where all HIV medications were stopped without guidance from an HIV primary care provider. Using these measures, a composite index of ART adherence and persistence will be calculated by summing the following indicators (1 point each): 1) currently on ART; 2) no treatment interruption in the past six months; and 3) 100 % self-reported ART adherence in the past 30 days.

#### Psychological adjustment

The Differential Emotions Scale (DES) is administered to assess the frequency of positive and negative affect during the past week [54]. Participants rate how frequently they felt a particular emotion during the past week. The DES measures high and low level intensity positive and negative affect, which will be examined as separate outcomes. The Center for Epidemiological Studies Depression Scale (CES-D) is administered to measure symptoms of depression during the past week [55, 56].

#### Stimulant craving

The Penn Alcohol Craving Scale is a five-item self-report measure that was adapted for assessment of methamphetamine craving [57]. Frequency, intensity, and duration of thoughts about using methamphetamine are assessed at each assessment visit. Immediately before and after each individual session (i.e., ARTEMIS intervention or attention-control), participants also rate the intensity of their current craving for methamphetamine, powder cocaine, and crack cocaine separately using a visual analogue scale from zero (no craving at all) to 100 (some of the worst craving ever).

#### Stimulant use

Participants report how often they have used various substances in the past three months. Participants who have used a given substance in the past three months are asked to report the number of days they used that substance in the past 30 days, which is consistent with Addiction Severity Index [58]. Participants also report the longest number of days in a row they used each substance in the past 30 days to index binge use [59]. Finally, those who provide a urine sample that is reactive for methamphetamine or cocaine (1) will be compared to those who provide a urine sample that is not reactive for these stimulants (0).

#### Potentially amplified transmission risk behavior

Participants report the number of anal sex partners in the past 3 months, stratified by whether or not they were feeling the effects of methamphetamine [21]. The total number of condomless HIV-negative or unknown serostatus partners is calculated, stratified by methamphetamine use. Potentially amplified transmission risk partners are the number of condomless anal sex partners who are HIV-negative or unknown serostatus where participants have a HIV viral load greater than 200 copies/mL at the same assessment visit. The total number of potentially amplified transmission risk partners stratified by methamphetamine use will be calculated. We will also examine any engagement in any potentially amplified transmission risk as an outcome.

### Outcome analyses

We will first generate one-way frequency tables for all variables and measures of central tendency and variability for continuous variables (e.g., means, medians, standard deviations) to perform range checks, quantify the amount of missing data, and yield valuable descriptive findings. Chi-square tests, *t*-tests, and comparable two-group non-parametric tests will be used to investigate equality of potential confounders (e.g., homelessness) across the intervention and attention-control conditions at baseline. Similarly, we will confirm that there are no differences in the mean number of intervention and attention-control sessions completed as well as no differential attrition by study arm.

Based on our extensive experience working with this population, we anticipate a maximum of 20% attrition over the 15-month investigation period. Attrition analyses will compare respondents who complete all measurements to those who do not based on baseline characteristics and we will test for differential attrition by intervention condition. Direct maximum likelihood and multiple imputation will be used to address incomplete data because these methods make the relatively mild assumption that missing data arise from a conditionally missing-at-random process [60].

Intent-to-treat analyses will be conducted primarily using multilevel random coefficient models (i.e., hierarchical linear modeling; HLM). These models incorporate random intercepts and slopes for each participant based on the participant’s multiple measurements over time [61]. Initial models will be unadjusted and compare outcome trajectories for participants in ARTEMIS + CM and Attention-Control + CM across time via the group-by-time interaction effect. If preliminary analyses detect imbalance in potential confounders across the groups that cannot be satisfactorily addressed via covariate adjustment, we will substitute causal inference methods based on the Rubin causal model (e.g., propensity score weighting; marginal structural models) to obtain population-level effects of the intervention under the assumption of balanced confounders between the two groups [62–66]. A priori planned comparisons will be performed to test group differences at 3, 6, 12, and 15 months for both the primary and secondary outcomes. These planned comparisons will be evaluated at α = .05; any subsequent post-hoc comparisons will be adjusted via simulation-based stepdown methods to maintain a nominal Type I error rate of .05 [67].

The primary outcome will be log_10_ HIV viral load over the 15-month follow-up. Sustained HIV viral suppression will be examined as a secondary outcome using logistic regression of the binary outcome of sustained virologic suppression over the 15-month follow-up (0 = no; 1 = yes) on randomization group assignment. Other continuous secondary outcomes that will be examined in intent-to-treat analyses include: CD4+ T-cell count, positive and negative affect, stimulant craving, and self-reported stimulant use. Ordered categorical and categorical outcomes assessed repeatedly over the 15-month follow-up include: ART adherence and persistence, a positive urine toxicology result for stimulants, potentially amplified transmission risk partners stratified by methamphetamine use, and any potentially amplified transmission risk.

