### Run-in period and randomization

All eligible participants complete a run-in period where they are required to complete five separate visits prior to randomization. These visits include: 1) a baseline assessment with a peripheral venous blood sample; 2) three urine screening visits (regardless of the toxicology results) at the community-based CM program; and 3) a separately scheduled randomization visit where the first intervention or attention-control session is administered. Participants who fail to complete the run-in period are not randomized and do not complete subsequent visits for this RCT unless at some point they re-initiate contact with the study team and choose to be re-screened. Randomization is accomplished using a computer generated sequence with randomly permuted block sizes of 2, 4, and 6 to guard against subversion. Only the study data manager has access to the computer-based randomization algorithm. Because randomization occurs at the first intervention or attention-control session, this ensures that all participants in this RCT complete at least one of the five individually delivered sessions.

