### Power analysis

Using NCSS PASS with a total sample size of 150, 80 % retention, and four repeated measures of viral load, the minimum detectable effect sizes are in the small-medium range (Cohen’s *d* = 0.29–0.47). Estimates of the minimum detectable effect size vary depending on the within-subject correlation. Overall, this RCT has adequate power to detect moderate effects of ARTEMIS + CM on the primary outcome, log_10_ HIV viral load.

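### Baseline viral load is drawn from every participant before randomisation but is not pre-specified as an adjustment in the viral load or sustained-suppression models, at a moderate cost in efficiency

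*Protocol article*

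**What the plan says.** All references are to the protocol article.

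- **Repeated-measures model (Outcome analyses).** Random intercepts and slopes per participant. "Initial models will be unadjusted and compare outcome trajectories for participants in" the two arms, through the group-by-time interaction. Group differences at each follow-up visit are also planned: "These planned comparisons will be evaluated at α = .05".
- **Sustained suppression (Outcome analyses).** The method is "logistic regression of the binary outcome of sustained virologic suppression over the 15-month follow-up", with randomised arm as the only term.
- **Covariates (Outcome analyses).** Adjustment is mentioned only in connection with imbalance found in preliminary baseline tests. Baseline viral load is not named.
- **Availability of baseline (Run-in period and randomization).** Before randomisation each participant must complete "a baseline assessment with a peripheral venous blood sample". Under Follow-up assessments and specimen banking: "Peripheral venous blood samples are collected at baseline as well as 6, 12, and 15 months following enrollment in CM to measure HIV viral load".
- **Primary outcome.** The outcome measures section defines it as a change in mean log10 viral load. The abstract says mean viral load, and Outcome analyses says log10 viral load over follow-up.
- **Power analysis.** "Using NCSS PASS with a total sample size of 150, 80 % retention, and four repeated measures of viral load", the minimum detectable effect is d = 0.29 to 0.47, depending on a within-subject correlation that is not given.

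**The concern.** A pre-randomisation measurement of the outcome itself is usually the most useful covariate a trial has, and here it is already paid for. The text leaves it out of the logistic model. In the repeated-measures model it enters only as a response, and nothing says that the arms share a common mean before treatment starts. Where the arms are free to differ at baseline, the model spends information on estimating a difference that randomisation makes zero in expectation.

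Tying adjustment to observed imbalance also makes the final model depend on the results of baseline tests. With about 120 expected completers, what is at stake is precision on the primary outcome and power on the main virological secondary outcome.

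**Working it through.** **Inputs.** N = 150 and 80% retention come from Power analysis; "we anticipate a maximum of 20% attrition over the 15-month investigation period" (Outcome analyses) agrees. This leaves 120 analysed, or 60 per arm if allocation is 1:1. Viral load is drawn at 0, 6, 12 and 15 months. Alpha is 0.05. *Assumed:* two-sided test, 80% power (the article says only that "this RCT has adequate power to detect moderate effects" is present), compound symmetry with correlation ρ, and unit variance at each visit.

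**Step 1: the plan's own figure.** For the average of m measures, d = (1.960 + 0.842) × √(2/60) × √((1 + (m−1)ρ)/m). The first two factors give 0.511. With m = 4:
- ρ = 0.1: 0.511 × √(1.3/4) = 0.292
- ρ = 0.8: 0.511 × √(3.4/4) = 0.472

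This reproduces 0.29 to 0.47 and implies a range for ρ of about 0.1 to 0.8. In this formula a higher ρ makes the detectable effect worse, so it takes no credit for baseline adjustment.

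**Step 2: the planned interaction (linear slope).** Scale time as t = 0, 0.4, 0.8, 1, so Σt = 2.2 and Σt² = 1.8. With V the correlation matrix of the four measures:
- free baseline in each arm: variance = 2 / {n[t′V⁻¹t − (1′V⁻¹t)²/(1′V⁻¹1)]}
- common baseline mean: variance = 2 / (n·t′V⁻¹t)

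The proportion saved is therefore (1′V⁻¹t)² / [(1′V⁻¹1)(t′V⁻¹t)]. Under compound symmetry this reduces to 1.21(1−ρ)/(1.8 + 0.56ρ).

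| ρ (assumed) | Variance saved | Detectable 15-month difference, free → common baseline |
|---|---|---|
| 0.1 | 1.089/1.856 = 59% | 0.632 → 0.406 |
| 0.5 | 0.605/2.080 = 29% | 0.471 → 0.397 |
| 0.7 | 0.363/2.192 = 17% | 0.365 → 0.333 |
| 0.8 | 0.242/2.248 = 11% | 0.298 → 0.281 |

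In sample-size terms, 29% is 1/0.71 = 1.4 times and 11% is 1/0.89 = 1.1 times. The planned model also has random slopes. Adding a slope variance of 0.25 lowers the saving to 22.5% at ρ = 0.5 and 11% at ρ = 0.7.

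**Step 3: group difference at one visit.** The variance factor is 1 for a level, 2(1−ρ) for a change from baseline, and 1−ρ² with baseline adjustment. The saving is ρ² against a level and (1−ρ)/2 against a change.

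| ρ (assumed) | Saved vs level | Saved vs change | Detectable effect: level / change / adjusted |
|---|---|---|---|
| 0.1 | 1% | 45% | 0.511 / 0.686 / 0.509 |
| 0.5 | 25% | 25% | 0.511 / 0.511 / 0.443 |
| 0.8 | 64% | 10% | 0.511 / 0.323 / 0.307 |

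**Step 4: sustained suppression.** Simulated with 60 per arm, about 3,000 runs per row and a conditional log odds ratio of 1.2. All rates are assumed.

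| Suppressed at baseline | Sustained in controls: suppressed / not suppressed at baseline | Power, arm only → baseline-adjusted |
|---|---|---|
| 50% | 60% / 15% | 71% → 80% |
| 50% | 70% / 10% | 53% → 69% |
| 50% | 50% / 25% | 86% → 88% |
| 70% | 65% / 15% | 67% → 79% |

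Two further simulations used a conditional odds ratio of 3, 50–60% suppressed at baseline and a 70% / 10% split. They gave 42–45% → 59–60% (800 runs per scenario) and 45–48% → 63% (1,500 runs), with type I error about 5% for both models. The gain is in power, not in a smaller standard error. In the first row the standard error of the log odds ratio rises from 0.38 to 0.46, while the estimate moves from 0.93 to 1.23, because the adjusted odds ratio is conditional on baseline.

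**The case against.** The strongest reply is that the primary model already uses baseline. Four viral load measures can only be baseline plus 6, 12 and 15 months, the outcome is defined as a change, and an interaction contrasts trajectories from baseline. This stands, and it is why the saving on the slope is 11% to 29% at ρ of 0.5 to 0.8 and not more.

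A second reply is that calling the models initial leaves room for adjusted ones, and that a covariate list may sit in an analysis plan not shown. This stands in part. But the article does more than stay silent: it states unadjusted models and an arm-only regression, and it links adjustment to detected imbalance.

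A reader might infer three stronger things that the documents do not support.

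- *That the trial forgoes the equivalent of 1.6 to 2.6 times its sample size.* That figure compares baseline adjustment with an unadjusted mean of the three post-baseline visits at ρ of 0.5 to 0.7. The article plans no such test.
- *That chance baseline differences bias the result.* The interaction subtracts a baseline gap. In a level comparison such a gap adds variance, not bias, under randomisation.
- *That anyone detectable at entry fails the sustained-suppression endpoint.* The abstract does count four blood samples over the 15-month follow-up, which includes baseline. The follow-up section, however, lists follow-up assessments at 3, 6, 12 and 15 months only. The wording is ambiguous; it does not show that baseline counts.

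**Conclusion.** The point holds as one of efficiency. No stated model pre-specifies adjustment for baseline viral load, although the value should exist for every randomised participant.

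- **Interaction test:** a moderate loss, about 29% of the variance at ρ = 0.5 and 11% at ρ = 0.8. It is larger only if ρ is low.
- **Visit-specific differences:** the size depends on whether they are levels or changes, which the text leaves open. The loss is 1%, 25% and 64% for levels, and 45%, 25% and 10% for changes, at ρ of 0.1, 0.5 and 0.8.
- **Sustained suppression:** roughly 2 to 18 points of power, depending on assumed rates.

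The unadjusted analyses are valid. The sizes rest on a correlation and suppression rates that the article does not give, and on compound symmetry, 1:1 allocation, 80% power and a two-sided test.

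**What to change.** 1. Pre-specify, whatever baseline imbalance is seen, that the primary model constrains the arms to a common baseline mean. An alternative is baseline log10 viral load as a covariate, with outcomes at 6, 12 and 15 months.
2. Add baseline detectability or baseline log10 viral load to the sustained-suppression logistic model. Report a standardised risk difference beside the odds ratio, because the adjusted odds ratio answers a conditional question.
3. State that sustained suppression is judged on the post-randomisation draws at 6, 12 and 15 months.

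This needs no new data or visits. The cost is the wording, settling the models before outcome data are examined by arm, and a sentence explaining the conditional odds ratio.
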